### Analysis of Expectation and Engagement

We use the same linear mixed-effects analysis for the Stroop task analysis. For the rating of expectation and engagement, we enter physical exercise intensity (high/low), video game (Brain Age/Tetris), week (0, 1, 2, 3, 4), age (60–70 years), and gender (male/female) as fixed effects into the model. As random effects, we have intercepts for participants, as well as by-participant random slopes for the effect of physical exercise intensity and video game. Experimental and control condition are compared whether any significant differences exist in expectation and engagement between the experimental condition (high intensity, Brain Age) and the control condition (low intensity, Tetris) and for expectation whether the answers changed significantly before and after the intervention.

### Analysis of Physical and Game Performances

To check the exercise intensity in all conditions, we calculate average heart rates during the high and low-intensity exercise. We will check that the average heart rates will be around 90%HRmax for high intensity or at 60%HRmax for low intensity. In addition, we use the same linear mixed-effects model analysis for the expectation and engagement. We expect that the effect of the physical exercise intensity will be found.

For the game performance, we will separately calculate the average game scores of Brain Age and Tetris. For Brain Age, we will use the average time to solve 100 simple arithmetic calculations and read aloud sentence. For Tetris, we will use the average game scores. Then, we will conduct linear mixed-effects analysis for each game score separately. For the average time of Calculate × 100 and the Reading aloud games in Brain Age, we enter physical exercise intensity (high/low), age (60–70 years), week (1, 2, 3, 4), and gender (male/female) as fixed effects into the model. As random effects, we have intercepts for participants, as well as by-participant random slopes for the effect of physical exercise intensity. For the average score of Tetris, we will use the same model as the Brain Age analysis. We will check any significant difference in the exercise condition.

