## Methods

### Trial Design, Setting and Registration

This study is a randomized crossover controlled trial to test the response of Stroop task performance (cognitive task for executive function) and the related brain activity using fMRI to an acute bout of high-intensity physical exercise followed by a short session with a brain training video game in physically active and cognitively healthy older adults (60–70 years). In four sequentially applied interventions, the participants will undergo every one of the four combinations of experimental and control conditions (Figure 1). Participants are blind to the study’s hypothesis. The Consolidated Standards of Reporting Trials (CONSORT) statement (Moher et al., 2010) as well as the Standard Protocol Items: recommendations for Interventional Trials (SPIRIT) statement (Chan et al., 2013) were used as a framework for developing the study methodology (see Supplementary Tables S1–S3). For CONSORT, the extension for within-subject design (Pandis et al., 2017) as well as the extension for non-pharmacological trials (Boutron et al., 2017) have been considered.

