### Sample Size

Calculation of the sample size is not possible because no similar study has been reported to date. Soares et al. (2016) report that the optimal sample size for adequate reliability and power in fMRI studies might be between 16 and 32 participants. Zysset et al. (2007), who also conducted an experiment with Stroop task in fMRI, respectively used 23 and 24 participants per group. We also aim to include 24 participants.

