### Interventions Overview

To check whether the participants can perform moderate to vigorous exercise and as already conducted in other studies (Knowles et al., 2015; Hwang et al., 2016; Grace et al., 2018), the participants will attend the familiarization phase over the course of 1 week and three sessions in all. Training at the first session is only performed at moderate intensity. The duration at high intensity is increased gradually for the second and third session. At the end of each session, the participants also practice the Stroop task and the video games for a total of 15 min. In the following intervention phase, each participant will sequentially perform four interventions with one intervention per week (four interventions after 4 weeks in all). The interventions are conducted once a week because reports of earlier studies state that to achieve a sufficient recovery in older adults, a break of at least 5 days is necessary between high-intensity physical exercise sessions (Herbert et al., 2015). Every intervention consists of a warm-up for the Stroop task to prevent the learning effect (Green et al., 2014). Each is followed by the actual physical exercise at either high or low intensity. After physical training, the participants go to the next room, where they can sit down and directly start the video gaming session with either the brain training video game “Brain Age” or with “Tetris.” The intervention is finished by the fMRI session using the Stroop task to investigate its related brain activity. Because there are two variables with two levels each, the possible combinations sum up to a sequence of four different interventions that one participant must undergo in a Latin square counterbalanced order (see Figures 1, 2). Each week, all participants will perform interventions one after another from morning until evening on two consecutive days. Participants are instructed to avoid strenuous physical activity during the 48 h (Knowles et al., 2015) preceding each intervention session. Each participant is also asked to refrain from food for 1.5 h and to have only a light meal beforehand, to refrain from caffeine and alcohol for 24 h (Knowles et al., 2015) before each intervention. Participants are asked to maintain their current lifestyle and not to make any changes to their level of physical activity or diet (Coetsee and Terblanche, 2017b).

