## Outcome

The primary outcome measures for all participants are the reaction time and correct answer count from the Stroop task as well as its related brain activity using fMRI after each of the four interventions. Additionally, the secondary outcome measures will be recorded similarly to the scores from the questionnaires for engagement after each intervention, the expectation after the familiarization phase and after the intervention phase, age, and gender at the first meeting.

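### The Brain Age and Tetris score models cannot be fitted as written: with two averaged scores per participant, a random intercept plus a random intensity slope leaves the slope variance inseparable from the residual

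*Protocol article*

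**What the plan says.** All of this is in the protocol article.

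- Trial Design, Setting and Registration: "the participants will undergo every one of the four combinations of experimental and control conditions". Interventions Overview: "each participant will sequentially perform four interventions with one intervention per week". Each combination of intensity and game therefore occurs once per participant.
- Sample Size: "We also aim to include 24 participants". The number rests on precedent, since "Calculation of the sample size is not possible because no similar study has been reported to date".
- Analysis of Physical and Game Performances reduces Brain Age to average times and Tetris to average scores. It continues: "Then, we will conduct linear mixed-effects analysis for each game score separately". The fixed effects are intensity, age, week and gender. The random effects are participant intercepts and "by-participant random slopes for the effect of physical exercise intensity. For the average score of Tetris, we will use the same model" as for Brain Age. The purpose is to see whether game performance differs by exercise condition. No simpler random-effects structure is named as a fallback.
- Stroop Task Analysis names R and lme4 for the mixed models. The game-score paragraph names no other software.

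**The concern.** A by-participant slope for intensity can be estimated only if each participant contributes more than one observation at one or both intensity levels, or if something else pins down the residual variance. Here each participant has one averaged score at high intensity and one at low. A person-specific intercept and slope already reproduce those two values exactly, so nothing is left from which to estimate residual error.

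The model is a definite specification that does not fit the data it is meant for, so this is more than missing detail. The analyst would meet an error and would have to change the random-effects structure, or override the software's check, after the data are in and without a rule to follow.

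**Working it through.** **Inputs.** 24 participants (Sample Size); four sessions each, one per intensity-by-game combination (Trial Design; Interventions Overview); one averaged value per score per session, a separate model per score, and a random intercept plus intensity slope (Analysis of Physical and Game Performances). The article states no observation count for these models, so there is no figure of its own to reproduce beyond the 24.

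**Count.** Sessions per game per participant: 4 / 2 = 2. Observations per model: 24 × 2 = 48. Random effects per model: 24 × 2 = 48.

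**Variance parameters.** Let s0 be the intercept variance, s1 the slope variance, s01 their covariance and se the residual variance, with intensity coded 0 (low) and 1 (high). Then:

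- Var(low) = s0 + se
- Cov(low, high) = s0 + s01
- Var(high) = s0 + s1 + 2·s01 + se

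That is three equations in four unknowns. The matrix of derivatives has rank 3 of 4.

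**Illustration (arbitrary values).** Four different parameter sets give the same covariance matrix [[120, 90], [90, 150]]:

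| se | s0 | s1 | s01 | Var(low) | Cov | Var(high) | s1 + 2·se |
|---|---|---|---|---|---|---|---|
| 0 | 120 | 90 | −30 | 120 | 90 | 150 | 90 |
| 10 | 110 | 70 | −20 | 120 | 90 | 150 | 90 |
| 20 | 100 | 50 | −10 | 120 | 90 | 150 | 90 |
| 30 | 90 | 30 | 0 | 120 | 90 | 150 | 90 |

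No data can choose between these rows.

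**What stays estimable.** The variance of the within-person high-minus-low difference is s1 + 2·se, which is 90 in every row. With 24 complete pairs the standard error of the intensity effect is √(90/24) = 1.936, whichever row is true. With a random intercept only, the residual variance absorbs half the slope variance: se* = se + s1/2 = 45, and 2·se* = 90 again. Adding week, as a linear term or as a factor, left the standard error at 1.936 under both structures. That was checked for alternating high/low Latin squares with six participants per sequence, which is an assumption because the sequence figure is not shown.

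**Simulation (24 participants, assumed alternating Latin square, arbitrary variances).** Fixing the residual variance at 0.01, 5, 10 or 20 gave the same REML objective (124.48627), the same intensity estimate (3.695) and the same standard error (1.585). The slope variance moved from 60.28 to 20.30 to compensate. At a residual variance of 30 the objective was slightly worse (124.49674), so the data bound the residual variance from above but do not determine it.

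**Software.** On simulated 24 × 2 data, lme4 1.1.37 stopped with an error that the 48 observations do not exceed the 48 random effects. The random-intercept model fitted.

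**Comparison.** The four-session models for engagement and heart rate, with intercept, intensity and game slopes, have 24 × 4 = 96 observations, 24 × 3 = 72 random effects and rank 7 of 7. They are identified.

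**The case against.** The best counter-argument is that the unidentified quantity is a nuisance. The covariance of the two scores is identified, so the likelihood, the intensity estimate, its standard error and the test are the same for every admissible split. The failure is also loud: the software stops, the remedy is obvious, and no silently wrong answer results. This stands. A reader might infer that any result from these models would depend on software defaults. The calculation does not support that for the intensity effect, which is the only thing this section sets out to examine.

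It also stands that game scores appear in none of the primary or secondary hypotheses and not in the Outcome section.

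A third argument is that participants repeat the games according to their speed (Video Game Intervention), so several runs per session may exist, and run-level data would identify the slope. That is true with at least two runs per session (rank 4 of 4). The analysis text speaks of averages, however, and the number of runs is not given, so this does not rescue the model as written.

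A reader might also extend the point to Analysis of Expectation and Engagement, which says "For the rating of expectation and engagement, we enter physical exercise intensity (high/low), video game (Brain Age/Tetris), week (0, 1, 2, 3, 4" although expectation is collected at two times only, "the expectation after the familiarization phase and after the intervention phase". The article does not support calling that an error. Weeks 0 to 4 can be read as the two rating schedules combined in one sentence, the before/after comparison for expectation is already stated there, and the questionnaire layout is not shown.

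**Conclusion.** The point holds for the Brain Age and Tetris score models only. Each has 48 observations against 48 random effects, and four variance parameters for three covariance elements. As specified, the check of exercise intensity on game performance cannot be run in lme4 at default settings. The intensity estimate and standard error are not distorted by the unidentified split, the four-session engagement and heart-rate models are identified, and nothing here touches the primary Stroop model.

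Severity is minor: this is a supporting analysis with a visible failure and a simple remedy.

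The conclusion assumes one averaged value per score per session, an unrestricted intercept–slope covariance (the article states no constraint), and lme4 for this analysis as for the Stroop model. Fewer than 24 participants would not help: each complete participant adds two observations and two random effects, and a missed session leaves one observation for two random effects.

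**What to change.** In Analysis of Physical and Game Performances, remove the by-participant intensity slope from the Brain Age and Tetris score models. Use a random intercept for participant, with intensity, week, age and gender as fixed effects. With two values per participant this is in effect the week-adjusted paired comparison, and its standard error already contains any between-person variation in the intensity effect.

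Alternatively, keep the slope and state that run-level scores are analysed, with at least two runs per session. That gives at least 24 × 2 × 2 = 96 observations per model, but it depends on how many runs participants complete, which the article does not give.

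The cost is a sentence or two of analysis text. The first option needs no new data and loses no precision for the intensity effect. It gives up only a separate estimate of the slope variance, which the averaged data could not provide. The random effects of the four-session models need no change on this account.

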### fMRI Analysis

Functional imaging data preprocessing and analysis were performed with Statistical Parametric Mapping SPM12 (Wellcome Trust Centre for Neuroimaging, London, UK). In the preprocessing, all functional images were corrected for motions using realign, co-registered to T1-weight structural image, then spatially normalized into the Montreal Neurological Institute (MNI) template. These normalized images were spatially smoothed using a Gaussian kernel of 8-mm full width at half maximum (FWHM).

All preprocessed functional images were analyzed using two-step statistics at the subject level and the group level. In the subject-level (fixed-effect) analyses, experimental trials were divided into two conditions (congruent and incongruent). Then, brain activations associated with these conditions and six motion parameters (three translational and three rotational directions) were modeled by convolving a vector of task onsets with a canonical hemodynamic response function (HRF) in the context of the general linear model (GLM). Low-frequency components of fMRI time series were removed by high-pass filtering. For each subject, the incongruent trials were contrasted to the congruent trials. All contrasts yielded a *t*-statistic in each voxel.

The contrast images from the first-level analysis were used for the second-level analysis (Random Effect). We analyzed the data using a 2 × 2 repeated measures analysis of variance (ANOVA) to assess the main effects of A (physical exercise: high intensity vs. low intensity), B (video game: Brain Age vs. Tetris), and the A × B interaction using the flexible factorial approach in SPM12. We used a threshold of *P*-value using whole-brain cluster family-wise error (FWE) correction at *P* < 0.05, with an uncorrected voxel-level cluster-defining threshold of *P* < 0.001.

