## Hypothesis

### Primary Hypotheses

Acute intervention with high-intensity physical exercise leads to significantly shorter reaction time at the Stroop task compared to intervention with low-intensity physical exercise.Acute intervention with the brain training video game Brain Age leads to significantly shorter reaction time at the Stroop task compared to intervention with the Tetris video game.Because an acute intervention of physical exercise might have a stronger effect on cognitive function than video gaming (McMorris and Hale, 2012; Bherer, 2015), the order for the other interventions with regard to the reaction time at the Stroop task is from short to long reaction time: (1) High intensity + Brain Age; (2) High intensity + Tetris; (3) Low intensity + Brain Age; and (4) Low intensity + Tetris.Acute intervention with high-intensity physical engenders stronger activations in DLPFC, VLPFC, and FPA compared to low-intensity physical exercise.Activation of R-FPA correlates with the performance (inversely with reaction time) at the Stroop task.Acute intervention with Brain Age video game leads to significantly different activation patterns from those obtained from intervention with Tetris video game, which also correlates with better performance at the Stroop task.

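### The fMRI group model leaves out week, tests the named-region hypothesis only through a whole-brain search, and gives no analysis for the R-FPA correlation

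*Protocol article*

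**What the plan says.** The Outcome section makes Stroop-related brain activity a primary outcome alongside reaction time and correct answers. Two of the primary hypotheses name regions. The fourth says that high-intensity exercise "engenders stronger activations in DLPFC, VLPFC, and FPA compared to low-intensity physical exercise". The fifth says: "Activation of R-FPA correlates with the performance (inversely with reaction time) at the Stroop task". The sixth predicts different activation after Brain Age than after Tetris, linked to better Stroop performance, and names no region.

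The fMRI Analysis section takes the incongruent-minus-congruent contrast from each session to the group level. There: "We analyzed the data using a 2 × 2 repeated measures analysis of variance (ANOVA) to assess the main effects of A" (exercise) and B (game), "and the A × B interaction using the flexible factorial approach in SPM12". Inference is fixed as well: "We used a threshold of *P*-value using whole-brain cluster family-wise error (FWE) correction at *P* < 0.05". Clusters are formed at a voxel-wise P of 0.001 before correction. The section names no week or period factor, no region of interest, no small-volume correction and no model relating activation to behaviour.

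Elsewhere, week is a fixed effect in the models for Stroop performance, for expectation and engagement, and for exercise and game performance. Interventions Overview schedules one intervention per week for four weeks, each ending in a scan. Randomization sets a four-sequence Latin square with high and low intensity alternating. Allocation and Implementation assigns participants to sequences from a random number list and does not state equal numbers per sequence.

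**The concern.** There are two separate problems.

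**Week.** The design changes condition every week. The analysis sections treat week as worth adjusting for in every mixed model but not in the fMRI group model. If the interference contrast drifts over four scans, for instance through practice, that variation is left in the error term of a primary outcome. The sample size is 24, chosen by precedent without a power calculation, so there is no known reserve of power to absorb the loss.

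**Fit between hypotheses and tests.** The fourth hypothesis is a directional statement about three named areas, but the stated inference searches the whole brain. The fifth is a brain-behaviour correlation, and no analysis is given for it. The same gap affects the part of the sixth hypothesis that links activation to performance. Leaving the regions and the correlation model open on a primary outcome allows choices to be made after the maps are seen.

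**Working it through.** The article gives no power, effect size or SD for the fMRI outcome, so there is no figure of its own to reproduce. Drift and effect sizes below are assumptions.

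**Inputs.** From the article: 24 participants, 4 weekly scans each, three group-level effects (A, B, A × B), alternating high/low Latin square. Assumed: 6 participants per sequence, a linear drift of *b* residual SD per week, residual SD 1.

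**Degrees of freedom.** Observations: 24 × 4 = 96. Without week: 96 − 24 − 3 = 69. With week: 69 − 3 = 66.

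**Residual variance without week.** With weeks coded 0 to 3, the squared deviations from 1.5 sum to 2.25 + 0.25 + 0.25 + 2.25 = 5. With equal sequences, week is orthogonal to A, B and A × B, so all of the drift goes to the residual: 24 × 5 × *b*² = 120*b*². The variance multiplier is 1 + 120*b*²/69.

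Power (two-sided 0.05, assumed true effect 0.6 residual SD) and type I error come from 20,000 simulated data sets per drift:

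| Drift *b* per week | Variance × | SE × | Type I error, no week | Power, no week | Power, week added |
|---|---|---|---|---|---|
| 0.1 | 1 + 1.2/69 = 1.02 | 1.01 | 0.051 | 0.82 | 0.82 |
| 0.25 | 1 + 7.5/69 = 1.11 | 1.05 | 0.041 | 0.80 | 0.82 |
| 0.5 | 1 + 30/69 = 1.43 | 1.20 | 0.021 | 0.71 | 0.82 |
| 1.0 | 1 + 120/69 = 2.74 | 1.66 | 0.001 | 0.37 | 0.82 |

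Bias in A and B was 0.000 throughout. The same result came from two different alternating squares.

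**Unequal sequences.** A participant scanned high-low-high-low has high sessions at weeks 0 and 2 (mean 1) and low sessions at weeks 1 and 3 (mean 2). The high-minus-low difference therefore carries −*b*; the reverse order carries +*b*. Across the trial:

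bias in A = *b* × (number starting low − number starting high)/24.

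A 14 to 10 split, for example, gives *b* × 4/24 = 0.17*b*. If each participant is allocated independently with equal chance, the SD of this bias is *b* × √24/24 = 0.204*b*, that is 0.05, 0.10 and 0.20 at *b* = 0.25, 0.5 and 1.0. Simulation with 3,000 trials gave 0.05, 0.10 and 0.21. For scale, the standard error of the exercise contrast with equal sequences and no drift is √(2/48) = 0.204. At *b* = 0.5 the typical chance bias is thus about half a standard error. Averaged over possible allocations, type I error still stayed below 0.05 (0.042, 0.035, 0.023).

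**Hypotheses against stated tests.**
- Fourth (DLPFC, VLPFC, FPA, high above low): the main effect of A over the whole brain covers these areas, but the correction pays for the entire search volume.
- Fifth (R-FPA with reaction time): no analysis is given. The only other fMRI analysis in the article is a correlation with engagement, made only if engagement differs (Expectation and Engagement); it tests none of these hypotheses.
- Sixth (Brain Age against Tetris, no region): the main effect of B over the whole brain is a suitable test of the difference in activation.

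**The case against.** The strongest reply on week is that the Latin square already balances it, that habituation common to both trial types cancels in the incongruent-minus-congruent contrast, and that repeated practice is planned to limit learning. A drift of 0.5 SD per week means 1.5 SD between the first and last scan, which may be large for such a contrast; at 0.1 the loss is negligible. All of this stands as a limit on size. It does not explain why the fMRI model should omit a term that the other models carry, when the term costs 3 df.

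On regions, the reply is that whole-brain cluster FWE is conventional and stringent, that it includes the named areas, and that region coordinates and secondary regressions are often left to a fuller plan. The first two parts stand. The third stands only in part: the section fixes model, search volume and threshold, and the Dissemination Policy says the article is meant to serve as the full protocol.

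A reader might infer more than the documents support:
- *That the named regions are not tested at all.* They are, through the main effect of exercise. A cluster lying in DLPFC would support the fourth hypothesis.
- *That omitting week inflates false positives.* It lowers the type I error, and with equal sequences it causes no bias.
- *That the R-FPA analysis would be circular.* Nothing says the region will be drawn from the trial's own data; the background cites earlier imaging work that could supply it.
- *That the loss of regional power can be quantified by setting the 0.001 voxel threshold against a single region test at 0.05.* That threshold only defines clusters, and inference is on cluster extent, so a single-voxel figure is not regional power. The article gives nothing from which the loss could be calculated.

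**Conclusion.** The concern holds in a limited form. The fMRI group model omits week, against the practice of the article's own mixed models. The cost is lost precision: residual variance × 1.02 to 1.43 for assumed drifts of 0.1 to 0.5 SD per week, and power from 0.82 down to 0.71 at the upper end for an assumed effect of 0.6 SD. Chance bias in the exercise contrast is possible if sequences end up unequal. Equal allocation is not stated, and later exclusion for a Stroop correct rate below 80%, or destruction of data on withdrawal, could also upset the balance. The size depends entirely on a drift that the article does not give.

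The mismatch between hypotheses and tests needs no numerical assumption. The fourth primary hypothesis has only an indirect test, generally less sensitive for the named areas than a search restricted to them, and the fifth has none. These are worth correcting before the data are analysed. They do not invalidate the design or the whole-brain analysis.

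**What to change.** 1. Add week as a four-level factor to the second-level model. Cost: 3 of 69 error df; in the calculation above, power without drift is unchanged at 0.82.
2. Define DLPFC, VLPFC and FPA before analysis from an atlas or published coordinates, stating whether left and right count separately. Test the fourth hypothesis in these regions, by mean contrast values or small-volume correction, with Holm correction over the stated number of regions.
3. Test the fifth hypothesis with a within-participant mixed model relating the contrast value in an independently defined R-FPA to Stroop interference reaction time over the four sessions, including week.
4. Keep the whole-brain FWE test as the confirmatory test for the sixth hypothesis (Brain Age against Tetris) and as supportive for the fourth. Making it merely exploratory would leave the sixth, which names no region, without a confirmatory test. State a model for that hypothesis's link with performance too.

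No extra scanning is needed. Beyond the 3 df, the cost is a little more analysis work and the need to commit to regions in advance. Averaging over a large region can dilute a focal effect, which is a reason to consider small-volume correction.
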